#### Measures to minimize bias: randomization and blinding

To guarantee adequate sequence generation and allocation concealment, centralized online randomization with 1:1 allocation to intervention or control group is done through REDCap. A person at the AMIB not further involved in the study creates randomization lists based on permuted blocks of random length and are stratified by age group (6–12, 13–17, ≥ 18 years) and FEV1 (≤ / > 60%) to guarantee nearly equal group sizes within the strata. Allocation concealment will be ensured, as the service will not release the randomization code until the patient has been entered into the trial, which takes place after all baseline measurements have been completed.

It is not feasible nor possible for the participating patients and most project staff to be blinded to treatment allocation. Primary outcome assessment will be based on patient reports. Staff who analyze the data will be blinded (arms will be designated randomly at that point as A and B). Data review will be performed blinded.

#### Populations for analyses

Three differing data sets are defined for the analyses:

Full analysis set

The full analysis set (FAS, based on the intention-to-treat (ITT) strategy) is defined to be all randomized patients according to their allocated intervention group, which fulfill the inclusion criteria and do not fulfill any exclusion criteria.

b)Per protocol set

The per protocol set (PPS) is defined by all patients belonging to the FAS without major violations of the study protocol. The following protocol violations are classified as major:Violation of an eligibility criterionDiscontinuation of intervention for non-medical reasonsNon-compliance

This is not an exclusive list. The full list of all major protocol violations, which will lead to the exclusion from the PPS, will be defined as part of the statistical analysis plan in the light of protocol violations which occur during study conduct. The final list of protocol violation will be finished before database closure and the beginning of the statistical analysis.c)Safety analysis dataset

The safety analysis set will include all randomized patients.

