**Methods:**

To test the main hypothesis, that an individualized and supported PA program leads to a better QoL 6 months after randomization (QoL-PCD questionnaire) compared to usual recommendation in pwPCD, 158 pwPCD aged 7 to 55 years are to be included in this multi-center randomized controlled trial (RCT). After the screening visit, a 1:1 randomization stratified by age group and FEV1 will be performed. A QoL-PCD questionnaire, motor test, and lung function will be carried out at regular intervals in both groups. PA is recorded in both groups using activity trackers during the study period. The main aim of the trial is to estimate the difference in the change of QoL between the groups after 6 months. Therefore, our full analysis set consists of all randomized patients and analysis is performed using the intention-to-treat principle. Statistical software R (http://www.r-project.org) is used. Ethical approvement without any reservations: RUB Bochum Ethics Committee (No. 23–7938; December 4, 2023). Recruitment start: March 2024.

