#### Inclusion criteria

To be eligible to participate in this study, an individual has to meet all the following criteria:Children and adolescents ≥ 7 years and adults ≤ 55 years oldConfirmed diagnosis of primary ciliary dyskinesia according to ERS criteria [21] (PCD confirmed or highly likely)Signed and dated informed consent form of the participants and of the guardian (in case of minors)Willingness to participate in the activity program and weekly phone contacts, and to wear the activity tracker for 1 year

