#### Study intervention discontinuation and participant discontinuation/withdrawal

The occurrence of diagnoses or examination results listed under “Exclusion criteria” or a positive answer in the weekly safety query described under “Safety assessments” will lead to an immediate discontinuation of the intervention.

When a subject discontinues from the PA program but not from the study, remaining study procedures will be completed as indicated by the study protocol. In individual cases, a decision may be made to continue the study without participation in the assessment of physical fitness.

In addition, all subjects are explicitly informed that if they have any doubts about PA and exercising, they should discontinue and contact the supervising or leading study center. Participants will be informed that if one of the following symptoms occurs, PA must be interrupted, or no further PA should be done until medical clarification is obtained:Fever or other infections accompanied by a feeling of illnessAcute pulmonary exacerbationSevere joint, back, or head pain during or immediately after exerciseChest pain or left arm painDizziness/syncopeShortness of breath (beyond expected level) or hyperventilationHypoglycemiaPersistent palpitations or heart palpitations after exercisePacemaker/ICD depending on type of PA

Participants are free to withdraw from participation in the study at any time upon request without giving reasons and without suffering any disadvantage, as stated to them prior to informed consent. Participants will be given the choice as to whether their withdrawal will only be from further contact from the trial team or withdrawal of all their unanalyzed data.

An investigator may discontinue a participant from the study for the following reasons:Lost-to-follow up; unable to contact subject (see below)Any event or medical condition or situation occurs such that continued collection of follow-up study data would not be in the best interest of the participant or might not be possible, e.g., longer inpatient stay

The reason for participant discontinuation or withdrawal from the study will be recorded on the study discontinuation form. Subjects who sign the informed consent form and are randomized but do not receive the study intervention may be replaced.

A participant will be considered lost to follow-up if he or she fails to return for one scheduled assessment and study staff are unable to contact the participant after five attempts.

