To minimize the risks for participating patients, they are examined in detail for contraindications to participation in a PA program (see schedule of activities and “Exclusion criteria”) and receive comprehensive information when not to take part in PA. In addition, the focus of this study is on health-enhancing, individually adapted physical activity and not on physical exertion. The participants do the PA they prefer at their own pace under the close guidance of the qualified personal trainer. For this reason, the intervention group is questioned weekly by means of a standardized questionnaire about the occurrence of potentially critical complaints in the context of PA by the respective personal trainer. If one of the participants answers at least one of the questions in the lower third of the Numeric Analog Scale [1–4, 21, 29, 37, 40, 48, 49], which is handed out and explained at V0, PA will be discontinued immediately until medical clearance by the lead study center in Bochum is obtained. A standardized safety questionnaire must also be completed before the motor test that is part of the study visits. If there are indications of a medical concern, the lead study center Bochum will be contacted and if there is any doubt the test will not be performed.

An assessment of adverse events (AE) and serious adverse events (SAE) will be performed in the intervention and control group to evaluate the safety of the study intervention. For further details see below and under “Safety oversight.”

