#### Analysis of the primary endpoint

The main aim of the trial is to estimate the difference in the change of quality of life between the intervention and control after 6 months in the domain of physical function. The confirmatory analysis will be conducted in the FAS based on the ITT principle. The analysis of the primary endpoint is carried out using a linear model. In addition to the intervention group, the model also includes baseline FEV1, gender and the interaction between age group, and baseline quality of life as independent variables. Estimated difference and corresponding two-sided confidence interval will be reported. In case of missing primary outcome, multiple imputation will be done. Missing values will be imputed from baseline and all available data after baseline.

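### The full analysis set carries an eligibility clause that contradicts the all-randomised, intention-to-treat population promised for the primary test

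*Protocol article*

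**What the plan says.** The protocol article describes the population for the confirmatory test in three places:

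- Abstract, Methods: "our full analysis set consists of all randomized patients and analysis is performed using the intention-to-treat principle".
- Populations for analyses, under the full analysis set: labelled as intention-to-treat, but defined as "all randomized patients according to their allocated intervention group, which fulfill the inclusion criteria and do not fulfill any exclusion criteria".
- Analysis of the primary endpoint: "The confirmatory analysis will be conducted in the FAS based on the ITT principle".

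Two neighbouring definitions matter. The per protocol set (PPS) is drawn from the FAS by removing major violations, and breach of an eligibility criterion is the first one listed. The safety set has no such filter: "The safety analysis set will include all randomized patients".

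Four further passages concern what happens after randomisation:

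- The exclusion list marks pregnancy as a drop-out criterion during the study.
- The section on discontinuation and withdrawal begins "The occurrence of diagnoses or examination results listed under" the exclusion criteria, and makes such findings a reason to stop the intervention at once.
- Safety assessments: "the intervention group is questioned weekly by means of a standardized questionnaire about the occurrence of potentially critical complaints in the context of PA".
- Measures to minimize bias: neither patients nor most project staff can be blinded.

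**The concern.** The trial has one confirmatory test, and the article gives two incompatible rules for who is in it. An analyst following the abstract keeps a randomised patient who turns out to be ineligible; an analyst following the analysis section removes that patient. A result from the second set could not properly be reported as an intention-to-treat result.

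The clause also does not say when eligibility is judged. Excluding patients for facts fixed before randomisation is comparatively harmless if the check is the same in both arms. Excluding them for something that happens or is noticed afterwards is not, because allocation can influence both the event and the chance of noticing it.

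**Working it through.** **1. The definitions side by side.**

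| Place | Randomised but ineligible patient |
|---|---|
| Abstract, Methods | in the FAS |
| Populations for analyses, FAS | out of the FAS |
| Analysis of the primary endpoint | in, if the intention-to-treat principle is followed |
| Populations for analyses, PPS | must be in the FAS, since this is where the patient is removed |
| Populations for analyses, safety set | in the safety set |

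Only the FAS clause excludes this patient. It also conflicts with its own section: if the FAS has already dropped everyone who fails eligibility, nobody is left for the PPS item to remove. That item would have content only if the FAS clause and the PPS item were read at different time points, which the text does not say.

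**2. Time point.** The clause has none. The exclusion list and the discontinuation section both foresee criteria being met during the study. One inclusion criterion, "Willingness to participate in the activity program and weekly phone contacts", could also be re-judged after allocation, although the quality-control section treats refusal of the intervention as non-compliance, which is a PPS matter.

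**3. Detection by arm.** The weekly standardised questions go to the intervention arm only. Adverse events are queried in both arms at V2 to V4. Detection in controls is therefore less frequent, but not absent.

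**4. Size.** The plan states no figure for exclusions, so there is none to reproduce. The inputs below come from Sample size determination.

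- Target 15.2 points and SD 30.4, so the effect size is 15.2/30.4 = 0.5. A two-sided t-test at 5% needs 63.8 per group, so 64, with power 80.1%. This agrees with the plan.
- Planned recruitment is 158, or 158/2 = 79 per arm. (128/0.95 gives 135, not 158; that is a separate matter and does not affect this point.)

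Assumptions, none of them from the documents: no true effect; a fraction f of the intervention arm is removed and no controls; those removed score a gap g below the rest of their arm, with g = 0.5 SD (15.2) or 1 SD (30.4); no covariate adjustment.

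- Bias: b = f × g
- SE = 30.4 × √(1/79 + 1/(79(1 − f)))
- Two-sided type I error = P(Z > 1.96 − b/SE) + P(Z < −1.96 − b/SE)

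| f (patients) | b, g = 15.2 | b, g = 30.4 | Type I error |
|---|---|---|---|
| 2% (about 2) | 0.02 × 15.2 = 0.3 | 0.02 × 30.4 = 0.6 | 5.0–5.2% |
| 5% (about 4) | 0.05 × 15.2 = 0.8 | 0.05 × 30.4 = 1.5 | 5.3–6.1% |
| 10% (about 8) | 0.10 × 15.2 = 1.5 | 0.10 × 30.4 = 3.0 | 6.1–9.4% |

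Against 15.2 points the bias runs from 0.3/15.2 = 2% to 3.0/15.2 = 20%. Exclusions equal in number and kind in both arms would give no bias on this formula. Lost numbers are not the issue, since 158 are planned against 128 needed.

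**The case against.** A reader might infer that the plan drops the sicker intervention patients after randomisation and so tilts the primary result towards the programme. The strongest reply is that the clause is about eligibility at entry, and much in the article supports that:

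- The hospital recruitment procedure settles eligibility before randomisation.
- The discontinuation section says that an exclusion-list finding stops the intervention; it says nothing of removal from analysis. A patient who leaves the programme but not the study completes the remaining procedures.
- The Study intervention section wants patients who become unable to exercise to provide at least the primary endpoint, and missing primary outcomes are multiply imputed.
- The PPS removes discontinuation for non-medical reasons. That wording would make little sense if the FAS had already lost everyone stopped for a medical reason on the exclusion list.

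Nor do the documents show that findings would surface mainly in one arm. Spirometry is repeated at 3, 6 and 12 months with no difference between arms stated. The study ECG is done once, at baseline. Nothing says that the weekly questions cover pregnancy. Syncope, chest pain and dyspnoea remain plausible examples, but only if the clause reaches past randomisation. Data review is blinded, analysts see neutral group labels, and the list of major violations is closed before database closure. The primary model adjusts for baseline quality of life and FEV1, so part of any gap already present at baseline would be absorbed.

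These points stand, and they rule out the stronger reading as a finding. They do not remove the contradiction: read as entry eligibility only, the clause still conflicts with the abstract and still duplicates the PPS item. Blinded review also cannot undo unequal detection that happened earlier.

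**Conclusion.** The point holds as a contradiction in the definition of the primary analysis population. The abstract, the primary endpoint section and the PPS list all imply a FAS that includes ineligible randomised patients; the FAS clause excludes them.

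Bias towards the programme is a possibility that the undated wording leaves open, not something the documents show. It would require the clause to be applied to events after randomisation, exclusions to differ between arms, and the excluded patients to have different outcomes. The size cannot be computed from the documents. If only entry eligibility is meant, few exclusions are expected after screening and the effect is probably small. The range of 0.3 to 3.0 points rests wholly on the assumed one-arm exclusions and unadjusted gaps. The case for correction rests on the conflict between definitions, not on that range.

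**What to change.** Define the FAS as all randomised participants, analysed in the arm to which they were allocated, regardless of eligibility violations, adherence or events after randomisation. Delete the eligibility clause. Keep eligibility violation as a reason for exclusion from the PPS only, where it then has content. Carry the same sentence into the SAP, and settle it before database closure.

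Reconcile the drop-out wording attached to pregnancy in the exclusion list with the continued follow-up described under Study intervention and in the discontinuation section, so that it is clear whether outcome data are still collected. How such participants are managed clinically is outside this point.

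The cost is one sentence in each document. No sample-size figure changes. A few ineligible participants may stay in the primary analysis, and the PPS analysis will show the result without them.

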### Statistical analyses

Statistical analysis will be performed using the statistical software R (http://www.r-project.org) version 4.1.0 or higher. Data scientists will remain blinded using non-meaningful group labels, e.g., the groups will be called “group A” and “group B.” For descriptive statistics, continuous variables will be summarized using the arithmetic mean and standard deviation; in case of skewed distribution, median and interquartile range are used. Categorical variables will be summarized using total counts and percentages.

Unless otherwise stated, the estimate with corresponding two-sided 95% confidence interval and two-sided *p* value will be reported for all confirmatory and exploratory analyses. *p* values less than 5% will be considered statistically significant. Details of the statistical analysis of primary and secondary endpoints, imputation of missing data, descriptive and additional analyses will be later specified in the statistical analysis plan (SAP). The following paragraphs give a basic overview of statistical procedures.

#### Analysis of the primary endpoint

The main aim of the trial is to estimate the difference in the change of quality of life between the intervention and control after 6 months in the domain of physical function. The confirmatory analysis will be conducted in the FAS based on the ITT principle. The analysis of the primary endpoint is carried out using a linear model. In addition to the intervention group, the model also includes baseline FEV1, gender and the interaction between age group, and baseline quality of life as independent variables. Estimated difference and corresponding two-sided confidence interval will be reported. In case of missing primary outcome, multiple imputation will be done. Missing values will be imputed from baseline and all available data after baseline.

#### Analysis of the secondary endpoint(s)

Analysis of all secondary outcomes will be done as complete case analysis, meaning that only cases with available data for the analysis are included. Analysis of the secondary efficacy outcomes will be undertaken following the same framework as the primary outcome model using appropriate generalized linear models.

For each continuous outcome, e.g., FEV1 and QoL-PCD, a linear regression model will be fitted, the intervention group, gender, FEV1 and the age group and the baseline value of the outcome considered were included as independent variables. For the QoL-PCD, an interaction term with age group is also added to the model.

For counting variables like number of pulmonary exacerbations, a similar generalized linear model will be fitted using a negative binomial distribution with a log link instead. Treatment effects are reported as relative risk with 95% confidence intervals.

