#### Adverse events and serious adverse events

In the following, we define the AEs and SAEs to which we are limited in this study due to the chosen intervention and the clinical characteristics of PCD. They comprehensively recognize both the expected risks and serious complications.

Adverse event (AE)Any unplanned doctor contactPulmonary exacerbation or other pulmonary complications (obstruction, etc.)New antibioticsAccident during physical activity without hospital contactMedically justified discontinuation of physical activity (single occurrence)Discontinuation of intervention due to a medical cause

Serious adverse event (SAE)DeathAny unplanned hospitalization or hospital presentation

For adverse events (AEs), the following guidelines will be used to describe severity.Mild—Events require minimal or no treatment and do not interfere with the participant’s daily activities.Moderate—Events result in a low level of inconvenience or concern with therapeutic measures. Moderate events may cause some interference with functioning.Severe—Events interrupt a participant’s usual daily activity and may require systemic drug therapy or other treatment. Severe events are usually potentially life-threatening or incapacitating. Of note, the term “severe” does not necessarily have to be identical with “serious.”

All adverse events (AEs) will have their relationship to study procedures, including the intervention, assessed by appropriately trained clinicians (pediatric and internal medicine) based on temporal relationship and his/her clinical judgment. The degree of certainty about causality will be graded using the categories below.Related—The AE is known to occur with the study procedures, there is a reasonable possibility that the study procedures caused the AE, or there is a temporal relationship between the study procedures and the event. Reasonable possibility means that there is evidence to suggest a causal relationship between the study procedures and the AE.Not related—There is not a reasonable possibility that the study procedures caused the event, there is no temporal relationship between the study procedures and event onset, or an alternate etiology has been established.

During each study visit (V2–V4), a standardized query (CRF) is made by means of questionnaires of the AEs and SAEs defined above. In addition, all participants are encouraged to report unplanned hospitalizations (SAEs) to their supervising study center within 48 h.

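### Secondary outcomes are fixed as complete-case, although the primary is imputed and the motor test can go missing for health reasons partly specific to one arm; separately, the count-model effect is a rate ratio, not a relative risk

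*Protocol article*

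**What the plan says.** Analysis of the secondary endpoint(s) sets the missing-data rule: "Analysis of all secondary outcomes will be done as complete case analysis, meaning that only cases with available data for the analysis are included". The models adjust for arm, gender, FEV1, age group and the baseline value of the outcome. For counts such as pulmonary exacerbations, "a similar generalized linear model will be fitted using a negative binomial distribution with a log link instead", and "Treatment effects are reported as relative risk with 95% confidence intervals".

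Analysis of the primary endpoint does the opposite for the physical functioning domain. It uses multiple imputation, and "Missing values will be imputed from baseline and all available data after baseline".

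The questionnaire, spirometry and the motor test are all scheduled at baseline and at 3, 6 and 12 months (Study assessments and procedures).

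Two sections say when the motor test may be absent:
- The section on study intervention discontinuation first covers participants who stop the activity program but stay in the study. It then says that, in individual cases, "a decision may be made to continue the study without participation in the assessment of physical fitness".
- Safety assessments requires a safety questionnaire before every motor test and omits the test if doubt remains. It also gives the intervention group, and only that group, a weekly safety query that can halt activity.

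**The concern.** The complete-case rule is a positive choice, not a gap left for the SAP, and it has two weaknesses.

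First, one questionnaire at one visit would give an imputed result for one domain and complete-case results for the others, on different sets of participants. No reason is given.

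Second, the motor test is a named secondary endpoint whose absence the protocol ties to poor health. Only the intervention arm has a program to stop and a weekly query that can stop it. If its less fit members drop out of the fitness comparison more often than their control counterparts, the remaining contrast favours the intervention. Lung function and fitness are the evidence for benefit beyond self-report, so a distortion there matters for interpretation.

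The label on the count outcomes is a separate matter. A reader who takes a ratio of mean counts as a risk ratio will misjudge how far the intervention changes the chance of having any exacerbation.

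**Working it through.** **What the plan gives.** It states no figure for missing secondary data. The only related figure is the 5% dropout in Sample size determination, and the total there does not follow from it: 2 × 64 = 128, and 128 / 0.95 = 134.7, so 135 rather than 158. The total of 158 implies 1 − 128/158 = 19%. I therefore take 5% (stated) to 19% (implied) as the range for missingness.

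**Bias of the complete-case contrast.** Simulation with no true effect and 1,000,000 participants per scenario. All coefficients are assumptions:
- 3-month value = 0.6 × baseline + 0.8 × noise.
- Outcome = 0.35 × baseline + 0.5 × 3-month value + 0.6 × noise, scaled to SD 1.
- Missingness is logistic with slope 1 on the variable named below, and its intercept is set to give the overall rate.
- The analysis regresses the outcome on arm and baseline among those observed.

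| Missingness depends on | Bias at 5% missing | Bias at 19% missing |
|---|---|---|
| baseline only | −0.001 SD | 0.000 SD |
| 3-month value, same way in both arms | −0.003 SD | 0.003 SD |
| 3-month value, opposite ways by arm | 0.033 SD | 0.114 SD |

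The first two rows are zero within simulation error. The third is a stress case. Dependence in the intervention arm only is milder and closer to the route that the protocol describes.

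A second simulation takes that form: 4,000 trials of 79 per arm, assumed correlations of 0.7 to 0.8 between visits, and 12.6% against 8.3% missing. Complete-case bias is 0.0445 SD with an SD of the estimate of 0.1217, so 0.0445 / 0.1217 = 0.37 standard errors. Using the 3-month value reduces the bias to 0.003 SD. The SD of the estimate becomes 0.1196, so the gain in precision is slight.

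**Rate ratio against risk ratio.** With mean count μ and dispersion k, a negative binomial count has P(at least one event) = 1 − (1 + kμ)^(−1/k). The documents give neither μ nor k. For an assumed rate ratio of 0.70:

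| Control μ | k | P(≥1), control | P(≥1), at 0.7μ | Risk ratio |
|---|---|---|---|---|
| 1 | 0.5 | 0.556 | 0.451 | 0.81 |
| 1 | 1 | 0.500 | 0.412 | 0.82 |
| 2 | 0.5 | 0.750 | 0.654 | 0.87 |
| 2 | 1 | 0.667 | 0.583 | 0.88 |

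With control means of 0.5 to 3 the range widens to 0.77 to 0.91. At means of 1 to 2, a 30% lower event rate is a 12% to 19% lower risk of any event.

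**The case against.** **Against bias.** The models adjust for baseline outcome, FEV1, gender and age group. Complete-case regression is unbiased if missingness depends only on arm and these covariates, and it is also about unbiased here if missingness follows 3-month status equally in both arms. The pre-test questionnaire applies to everyone, participants who stop the program are still meant to complete the remaining procedures, missed visits may be made up within 4 weeks, and skipping the fitness assessment is confined to individual cases. This stands to the extent that bias is possible and not certain, and that the health-related route concerns the motor test above all. It does not remove the route: the clause on skipping fitness assessment follows directly on stopping a program that only one arm has.

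**On method.** Imputing a confirmatory endpoint and not the secondary ones can be a deliberate hierarchy. For someone medically unable to do the motor test, imputation or a mixed model estimates performance as if tested, which is not self-evidently the right question. That is a real limit, to be stated alongside the analysis.

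**On the label.** The estimate itself does not change. Exacerbations are also defined as adverse events, which Safety analyses reports as number and percentage, so risks will be visible there. This limits the harm but does not make the label correct.

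**A stronger reading.** A reader might infer that the count model ignores time under observation, since no offset is mentioned. The article does not support this. It neither states nor excludes one, says that "The following paragraphs give a basic overview of statistical procedures", and defers details of the endpoint analyses to the SAP. If complete case restricts counts to full periods, follow-up is also nearly equal and an offset matters little.

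**Conclusion.** The point holds in two limited parts.

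1. The complete-case rule for all secondary outcomes is weaker than, and out of step with, the handling of the primary. It discards collected 3-month data and can bias the contrasts, the motor test most plausibly. The size ranges from about 0 to 0.03–0.11 SD, and the upper values rest on assumed missingness that works differently by arm. To say that the secondary estimates will be biased goes beyond the document.
2. Relative risk is the wrong name for the exponentiated coefficient of a log-link negative binomial model. The size of the possible misreading rests on assumed event means and dispersion.

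Both concern secondary analyses. The confirmatory result is untouched.

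**What to change.** In the SAP, analyse each continuous secondary outcome in one of two ways: with the multiple imputation already planned for the primary, or with a repeated-measures model using all visits (planned baseline covariates, visit, arm-by-visit, unstructured covariance). Keep complete case as a sensitivity analysis. For the motor test, report by arm how many tests were omitted for medical reasons, and state that the main estimate describes performance as if tested.

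Replace relative risk with rate ratio for the count outcomes. While editing that paragraph, it would help to state how partial counts are treated, because events are queried at each of V2 to V4.

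The cost is SAP wording and modest programming, with no new data. The analysis then relies on missing at random given the observed visits. The 3-month value helps only participants who reached that visit.
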